### 2.11. Laboratory Testing

Serum samples will be run on the Abbott ARCHITECT *i*1000SR instrument using the Abbott SARS-CoV-2 IgG assay in accordance with the manufacturer’s instructions. This is a CLIA for the qualitative detection of IgG in human serum or plasma against the SARS-CoV-2 nucleoprotein. Strength of response in relative light units reflects quantity of IgG present and is compared to a calibrator to determine the calculated index (specimen/calibrator [S/C]) for a sample (with positive at 1.4 or greater). This assay was independently evaluated for analytic performance and found to have a specificity of 99.9% from 1020 pre-COVID-19 serum specimens and a sensitivity of 100% at 17 days after symptom onset and 13 days after PCR positivity [19].

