Areas of uncertainty with SARS-CoV-2 antibody testing, is how long the IgG antibody levels remain detectable in the blood and the durability of humoral immune response post-infection. Early reports of serial antibody testing in recovering COVID-19 cases indicated an apparently short-lived antibody response. One study of 34 mild cases reported a half-life of 36 days for IgG levels measured over approximately 90 days [12]. In contrast, a recent seroprevalence study was performed on over 30,000 Icelanders, including 1797 RT-PCR confirmed COVID-19 cases, using six different antibody assays. This study demonstrated good IgG antibody durability, with levels rising to two months post-infection, and then sustained up to four months (the study cut-off) [13]. It is therefore unclear whether there are regional or ethnic variations in the durability of SARS-CoV-2 antibodies. The proposed study aims to estimate the cumulative SARS-CoV-2 infection rate and will further examine the durability of the humoral immune response specific to this virus in a cohort of HCWs in the Eastern Cape, South Africa.

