### 2.10. Nested Cohort Study (N_b_ = 201 Participants)

The sample size for the cohort study was estimated as 201 based on the expected proportion of HCWs (45% was reported in hospital setting in London by Houlihan et al. [2]) who could have acquired SARS-CoV-2 during the peak period of the pandemic. This sample was calculated at a 95% confidence level and confidence interval of 7.5. The final sample was adjusted in anticipation of a 27% attrition rate during the follow-up of the participants.

Only participants in category one will be pooled into the nested cohort study for serial antibody screening at eight-week interval to monitor the rate of decline in the antibody positivity rate (durability of SARS-CoV-2 specific humoral immune response). The participants in this sub-study will have blood samples drawn on two occasions; at baseline and final sample will be drawn at eight-week interval. Most studies have reported significant decline in the antibody levels by three to four months [12,13]. In anticipation of the challenges of follow-up study, participant recruitment will be based on their willingness to allow monitoring of their SARS-CoV-2 antibody levels. There will be no form of coercion of any HCW to participate or continue follow-up. Participants in this sub-study will receive text messages and face-to-face reminders on the date for blood tests.

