### 3.1. Primary Analysis (Point and Cumulative Seroprevalence)

Descriptive statistics (means ± standard deviations for continuous data and counts and proportions for categorical data) will be used to summarize the baseline (demographic and clinical) characteristics of the participants. Cumulative and point seroprevalence indicating the overall infection rate will be estimated. In addition, the case fatality rate per health facility will be estimated based on the total number of deaths of HCWs and the overall infection rate from this study.

The cumulative outcome (positive result obtained by either or both of SARS-CoV-2 RT-PCR and serology) will be described by fitting the univariate logistic model to examine the association with the individual covariates. In addition, multiple logistic regression models will be fitted to identify factors that are independently and significantly associated with the outcome measures. All variables will be included in the logistic regression model, then, variables with missing data will be excluded in the second model. Sensitivity analysis will be performed using complete data only, with an assumption that missing data would have occurred at random.

In addition, the symptom data will be correlated with the composite results of SARS-CoV-2 PCR and serology tests. An epidemiological curve will be constructed by including data of all infected HCWs with SARS-CoV-2 PCR-positive tests.

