### 3.2. Sub-Analysis (Longitudinal Changes in Antibody Detection)

Baseline detection of SARS-CoV-2 specific antibodies (IgG) will be summarized using descriptive statistics (counts and proportions for categorical data). HCWs with confirmed diagnosis with SARS-CoV-2 RT-PCR will be evaluated for the presence or absence of antibodies and the time interval between the two tests will be estimated. Durability of SARS-CoV-2 specific IgG antibodies will be assessed first by estimating the frequency (percentage) of the presence of antibodies and the mean (standard deviation) duration of persistence of the antibodies. Presence or absence of SARS-CoV-2 specific antibodies (IgG) (yes/no) at baseline will also be correlated with the disease severity.

Further, the nested cohort study will also provide additional answers regarding the durability of the humoral immune response. Baseline serology results of the 201 participants in the sub-study will be compared with the results of the subsequent serology test done at eight-week interval.

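### Seroprevalence is read as the overall infection rate with no allowance for IgG loss: infection is likely underestimated and fatality overestimated, less so on the PCR-or-serology composite

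*Protocol article*

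**What the plan says.** Section 3.1 states: "Cumulative and point seroprevalence indicating the overall infection rate will be estimated". The fatality rate per facility is to be "estimated based on the total number of deaths of HCWs and the overall infection rate from this study". The outcome carried into the regression models is broader: "The cumulative outcome (positive result obtained by either or both of SARS-CoV-2 RT-PCR and serology". A PCR-confirmed worker who has lost IgG is therefore still counted as infected there.

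For the chosen assay, Section 2.11 gives "specificity of 99.9% from 1020 pre-COVID-19 serum specimens" and "a sensitivity of 100% at 17 days after symptom onset and 13 days after PCR positivity". It gives no figure for later sampling.

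On persistence of IgG the article is mixed:
- Section 2.10: "Most studies have reported significant decline in the antibody levels by three to four months".
- The Introduction cites a study of 34 mild cases that "reported a half-life of 36 days for IgG levels measured over approximately 90 days". It then cites a much larger study, with 1797 PCR-confirmed cases, in which IgG rose for two months and held to four. It treats durability as uncertain.
- Section 2.9 provides a category for PCR-positive, seronegative participants, whose response did not persist or was not yet detectable.

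Section 3.2 will examine antibody presence in PCR-confirmed workers, and "the time interval between the two tests will be estimated". The article does not link that analysis to the infection rate in Section 3.1.

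**The concern.** The survey looks back over infections that may be months old, but the only performance figure for the assay comes from about two weeks after diagnosis. Reading seropositivity as past infection implicitly carries that 100% forward. If sensitivity has dropped by the survey, the infection rate is too low. With the number of deaths fixed, the fatality rate is then too high.

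The composite rescues only infections that happened to be PCR-diagnosed. The Introduction says PCR testing is often limited to symptomatic people and cites 46% asymptomatic infection. An infected worker who never had a positive PCR and has lost IgG falls into the Section 2.9 category of no confirmed infection. Undiagnosed infections are the ones the study was set up to find, because PCR counts miss them. Section 3.1 also leaves open whether the fatality denominator is the serology rate or the composite, and the two carry different amounts of bias.

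**Working it through.** The quoted 100% sensitivity comes from an outside evaluation with no numerator or denominator, so it cannot be reproduced. What can be checked is how far the reported rates would move if sensitivity at the survey were lower.

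**Inputs from the article.** Specificity Sp = 99.9% and cut-off 1.4 (Section 2.11); half-life 36 days and asymptomatic share 46% (Introduction); infection proportion 45% (planning value, Section 2.10).

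**Assumptions, not in the article.** Survey-time sensitivity Se = 70-90%; share f of infections with a previous positive PCR = 25-50%; an alternative true rate T of 20%; f independent of IgG loss; deaths fixed.

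**Formulas.**
- Serology only: T·Se + (1 − T)(1 − Sp)
- Composite: T·[1 − (1 − Se)(1 − f)] + (1 − T)(1 − Sp)
- Fatality inflation: T / observed rate

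Example, T = 45%, Se = 70%: serology 0.45 × 0.70 + 0.55 × 0.001 = 0.3156, and 0.45 / 0.3156 = 1.43. Composite with f = 25%: 0.45 × (1 − 0.30 × 0.75) + 0.00055 = 0.3493, and 0.45 / 0.3493 = 1.29.

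| True rate | Se | Serology only (inflation) | Composite, f = 25% | Composite, f = 50% |
|---|---|---|---|---|
| 45% | 90% | 40.6% (1.11) | 41.7% (1.08) | 42.8% (1.05) |
| 45% | 70% | 31.6% (1.43) | 34.9% (1.29) | 38.3% (1.17) |
| 20% | 90% | 18.1% (1.11) | 18.6% (1.08) | 19.1% (1.05) |
| 20% | 70% | 14.1% (1.42) | 15.6% (1.28) | 17.1% (1.17) |

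At Se = 100%, serology gives 45.05% and 20.08%, so there is essentially no bias. False positives add at most 0.1 percentage point and offset almost nothing.

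**A favourable case for the composite.** Suppose every symptomatic infection had a positive PCR, so f = 1 − 0.46 = 54%. Ignoring false positives, capture is 1 − 0.10 × 0.46 = 95.4% at Se = 90% and 1 − 0.30 × 0.46 = 86.2% at Se = 70%. Inflation is 1.05 and 1.16.

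**Is a lower sensitivity plausible?** With a 36-day half-life, IgG falls to 0.5^(90/36) = 18% of its starting level at 90 days and to 10% at 120 days. Time to the cut-off is 36 × log2(S/1.4): about 55 days from an index S of 4 and about 90 days from 8. These starting indices are assumed, as is an index proportional to IgG. Under the larger cited study, no such loss occurs up to four months.

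**Which correction fits which rate** (T = 45%, Se = 70%, f = 25%). The Rogan-Gladen estimate is (observed + Sp − 1)/(Se + Sp − 1).
- Serology only: (0.31555 − 0.001)/0.699 = 0.450, the true value.
- Applied to the composite as a whole: (0.3493 − 0.001)/0.699 = 0.498, an over-correction.
- Applied only to those without a positive PCR: these are 1 − 0.1125 = 0.8875 of the sample. Their seropositive share is (0.3375 × 0.70 + 0.55 × 0.001)/0.8875 = 0.2668, corrected to (0.2668 − 0.001)/0.699 = 0.380. The total is 0.1125 + 0.8875 × 0.380 = 0.450.

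**The case against.** The strongest defence is that the plan already contains the main remedy. The cumulative outcome counts a positive PCR as well as serology, and Sections 2.8 and 3 add laboratory and occupational-health records to fill gaps. This stands in part: it roughly halves the bias when half of infections were PCR-diagnosed, but it does nothing for point seroprevalence or for infections never diagnosed by PCR.

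Second, the waning evidence conflicts, and the larger cited study found IgG sustained to four months. This stands, and it is why the bias can be called likely but not certain. A reader might infer that infection is bound to be underestimated; the article does not support that.

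Third, an article may leave adjustment methods to a fuller plan, and Section 3.2 already looks at antibody presence by interval since PCR. That limits the criticism. But the article itself fixes the reading of seroprevalence as infection and ties fatality to it, so the point is not merely about missing detail. The Introduction also quotes a pooled 96.0% sensitivity at 21 to 35 days, but that covers many tests and is still early.

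A reader might also infer that the bias is larger in the antenatal women, distorting the comparison with healthcare workers. The article gives no PCR coverage for that group or by work area. If both groups are compared on serology with similar timing of infection, the ratio would hardly change.

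**Conclusion.** The point holds in a limited form. The plan equates seroprevalence with the overall infection rate and carries it into the fatality rate without allowing for IgG loss, while its own text anticipates such loss. The likely direction is infection too low and fatality too high.

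For an assumed survey-time sensitivity of 70-90%, fatality inflation is about 1.1-1.4 fold on serology alone. It is about 1.05-1.3 fold on the composite with an assumed 25-50% of infections PCR-diagnosed, and close to nil if IgG is sustained. Late sensitivity, time since infection and PCR coverage are not given, so these are illustrations, not estimates. A reader might take the 1.1-1.4 range as the error in the planned cumulative outcome; it applies to serology alone.

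**What to change.** In Section 3.1:

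1. Name the PCR-or-serology composite as the overall infection rate and as the fatality denominator.
2. Report beside it a sensitivity-adjusted rate over a stated range of survey-time sensitivities, running up to 100% to cover sustained IgG.
3. Inform that range from the study's PCR-positive participants (categories one and two of Section 2.9), by interval since PCR as Section 3.2 already plans. Staff never PCR-tested have no known infection date, so combine these figures with an assumed distribution of infection times, for example from the epidemic curve planned in Section 3.1.
4. Use Rogan-Gladen with 99.9% specificity for the serology-only rate. For the composite, apply the correction only to participants without a positive PCR.
5. Carry the uncertainty in sensitivity into the interval, and give the fatality rate under both the crude and the adjusted denominator.

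The cost is a short extra analysis on data already to be collected. The downsides are wider intervals and reliance on sensitivity from mostly symptomatic, PCR-confirmed cases. State the latter as a limitation without claiming which way it biases the adjusted rate, since nothing in the article settles that. The crude rate stays in the report.

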### 2.12. Main Outcome Measures

Seroprevalence of and factors associated with SARS-CoV-2 infection: overall infection rate and case-fatality rateFactors associated with durable SARS-CoV-2 specific IgG antibodies

## 3. Statistical Analysis

Data will be exported from Redcap to the STATA Version 15 (Stata Corp., College Station, TX, USA) and cross-checked for completeness and accuracy. Incomplete data will be re-verified, and where possible, the OHS and NHLS databases will be reviewed to maximize the chances that data for the main outcome measures are collated accurately. Multi-level analysis will be performed on all the participants; those with complete and incomplete results. Differences in the baseline (demographic and clinical) characteristics of the two groups will be compared by using Pearson chi-square and Fisher’s exact test for bivariate analysis.

### 3.1. Primary Analysis (Point and Cumulative Seroprevalence)

Descriptive statistics (means ± standard deviations for continuous data and counts and proportions for categorical data) will be used to summarize the baseline (demographic and clinical) characteristics of the participants. Cumulative and point seroprevalence indicating the overall infection rate will be estimated. In addition, the case fatality rate per health facility will be estimated based on the total number of deaths of HCWs and the overall infection rate from this study.

The cumulative outcome (positive result obtained by either or both of SARS-CoV-2 RT-PCR and serology) will be described by fitting the univariate logistic model to examine the association with the individual covariates. In addition, multiple logistic regression models will be fitted to identify factors that are independently and significantly associated with the outcome measures. All variables will be included in the logistic regression model, then, variables with missing data will be excluded in the second model. Sensitivity analysis will be performed using complete data only, with an assumption that missing data would have occurred at random.

In addition, the symptom data will be correlated with the composite results of SARS-CoV-2 PCR and serology tests. An epidemiological curve will be constructed by including data of all infected HCWs with SARS-CoV-2 PCR-positive tests.

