### 2.2. Participants

The study population will include all categories of HCWs at the selected health facilities. Given the large number of HCWs (doctors, nurses, allied health workers, and administrative staff) in the regional (about 1400 staff) and tertiary (about 1500 staff) hospitals in comparison to those in the primary health care (about 120 staff), it is expected that the majority of the participants in this study will be recruited from the two large hospitals. Since this cross-sectional study aims to provide mass screening (using a SARS-CoV-2 serological test) for all HCWs, about 2250 HCWs are expected to take part in this study. The estimated number of participants per study site is proportional to the overall count of HCWs at each site. A total of 750 antenatal women will be recruited from the study sites to provide data on the community infection rate. The recruitment of HCWs is pre-stratified for inclusivity and is proportionate to the total head count of staff in each facility as shown in Table 1.

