### 2.3. Study Procedure

All HCWs will be eligible to participate in this study. Using a multi-stage cluster sampling technique, participants’ clusters will be categorized by the facility of employment (Table 1) and exposure areas. Participants will be conveniently sampled within each cluster. Every HCW in each cluster will be given an equal opportunity to be sampled into the study, and participation will be purely voluntary.

Participants will be recruited from the study sites concurrently in order to avoid time variations in the main outcome measures. For inclusivity, exposure areas are pre-defined in accordance with risk assessment by Iversen et al. [4]:High risk: Accident and Emergency unit, acute respiratory (person under investigation/COVID-19) wards and intensive care units (ICU).Intermediate risk: non-respiratory admission wards, outpatient departments (OPDs) and other clinical areas.Low risk: administration offices and other non-clinical areas.

Information about this mass screening will be disseminated through the departmental heads and clinical managers. Each working areas/unit will be allocated specific days to give allowance for those on duty as well as those off-duty to participate with minimal interruptions in patient care. Each participant will complete a self-administered questionnaire. In addition, medical records of deceased HCWs during the pandemic will be reviewed in order to estimate the case fatality rate of HCWs in the study sites.

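### The risk-factor models in section 3.1 make no stated allowance for correlation within working units, so the standard error for exposure area would be too small

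*Protocol article*

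**What the plan says.** Protocol article, section 2.3, sets the sampling: "Using a multi-stage cluster sampling technique", with the statement that "clusters will be categorized by the facility of employment (Table 1) and exposure areas". The exposure areas are high, intermediate and low risk, each defined by type of ward or workplace. Within clusters, "Participants will be conveniently sampled within each cluster". Recruitment is run by workplace: "Each working areas/unit will be allocated specific days".

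Section 3.1 names the association models. The outcome, a positive PCR or serology result or both, is first described by "fitting the univariate logistic model to examine the association with the individual covariates". After that, "multiple logistic regression models will be fitted to identify factors that are independently and significantly associated with the outcome measures". No random effect, cluster-robust variance or survey method is mentioned.

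The only wording that might bear on clustering is in section 3: "Multi-level analysis will be performed on all the participants; those with complete and incomplete results". The sentence after it compares two groups by Pearson chi-square and Fisher's exact test.

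**The concern.** An ordinary logistic regression takes its standard errors from the assumption that participants are independent given the covariates. Staff of one ward share air, patients, PPE supply and each other's company, so their infection outcomes are plausibly correlated. Exposure area is constant within a unit. Any difference between units, such as one ward outbreak, is therefore counted by the ordinary model as evidence about exposure area.

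This matters because factors associated with infection are a main outcome (section 2.12). The Abstract promises conclusions on infection control by exposure site and ward, and section 7 says that area-specific rates might guide staff allocation. The Introduction reports that earlier studies disagree on whether work area or staff role matters, so a falsely significant area effect would mislead on an open question.

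**Working it through.** **Inputs from the document.** Section 2.2: "about 2250 HCWs are expected to take part in this study". Table 1 reproduces this figure: 1100 + 1000 + 75 + 75 = 2250. The document gives no error rate, ICC, unit count or design effect for the risk-factor models, so there is no stated figure of that kind to reproduce.

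**Assumptions.** Two-sided nominal level 5%; equal units of m = 20, 30 or 50 staff (about 112, 75 or 45 units); ICC from 0.005 to 0.05.

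**Formulas.** For a factor that is constant within units:

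- design effect DE = 1 + (m − 1) × ICC
- actual error rate = 2 × [1 − Φ(1.96 / √DE)]

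Example with m = 30 and ICC 0.02: DE = 1 + 29 × 0.02 = 1.58; 1.96 / √1.58 = 1.56; error rate 11.9%.

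| ICC | m = 20 | m = 30 | m = 50 |
|---|---|---|---|
| 0.005 | 6.1% | 6.7% | 7.9% |
| 0.01 | 7.2% | 8.4% | 10.8% |
| 0.02 | 9.5% | 11.9% | 16.4% |
| 0.05 | 16.0% | 21.1% | 29.1% |

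**Simulation check.** 4000 surveys per setting were simulated with no true area effect, assumed prevalence 20% and beta-binomial variation between units. The high-versus-low comparison, ignoring units, rejected as follows:

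| ICC | m = 20 | m = 30 | m = 50 |
|---|---|---|---|
| 0.005 | 5.7% | 7.1% | 7.1% |
| 0.01 | 7.5% | 7.7% | 10.8% |
| 0.02 | 9.8% | 11.6% | 15.5% |
| 0.05 | 15.9% | 21.0% | 30.2% |

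This agrees with the formula. The joint three-area test is affected more: 27.9% at m = 30 and ICC 0.05. With negligible ICC, the unadjusted tests reject 4.8% to 5.2% of the time. With unit-clustered standard errors, the high-versus-low test rejects 5.0% to 6.8% of the time at the positive ICCs simulated (0.005 to 0.10).

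**Person-level covariates.** Here DE = 1 + (m − 1) × ICC × ICC of the covariate. With outcome ICC 0.05 and covariate ICC 0 to 0.10, the error rate is 5.0% to 7.9% for m = 20 to 50. Factors such as age or comorbidity are therefore little affected.

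**The case against.** The strongest reply is that the defect is inferred from silence. A condensed article may say logistic regression and leave the variance method to a fuller document, and section 3 does use the term multi-level. Part of this stands: a reader might infer that the plan commits to independence, and it does not say so. But the only multi-level wording is attached to completeness of results, names no level, and is followed by tests that assume independence. Section 3.1, which fixes the models, does not pick it up. Even on the kindest reading, the two sections need reconciling.

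Three stronger readings are tempting and are not supported.

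- **Error always several times 5%.** This depends on ICC and unit size, neither of which is given. At ICC 0.01 or less with 20 to 30 staff per unit, the rate is about 6% to 8%.
- **The facility-by-area cells as the clusters.** Four facilities and three areas give at most 12 cells, a mean of 187.5 people each, and by the same formula 25% to 54% at ICC 0.01 to 0.05. If every cell is covered, the cells act as strata and not as sampled clusters. Working units are the recruitment rota, not a named sampling stage, so correlation within them is a modelling assumption, though a plausible one.
- **Overall seroprevalence far too precise.** At an assumed prevalence of 20%, the simple 95% half-width is 1.96 × √(0.2 × 0.8 / 2250) = 1.65 points. A design effect at ICC 0.02 would widen it to about 2.2 points (60 units) or 2.6 points (30 units). That treats units as a random sample from a wider population. Section 2.2 gives about 1400 + 1500 + 120 = 3020 staff, so 2250 is about 75% of the workforce surveyed. For prevalence in these four facilities with all units invited, variation between units is not sampling error. A finite-population correction would instead shrink the half-width to about 0.83 points.

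It is also fair that convenience sampling within purposively chosen facilities brings biases that no variance method repairs. That does not excuse standard errors that are too small.

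**Conclusion.** The concern holds for exposure area and other factors shared by a working unit. The stated models do not match the way staff are grouped and recruited, and the multi-level wording does not close the gap. At a nominal 5% level with 20 to 50 staff per unit, the actual error rate would be about 6% to 11% at ICC 0.005 to 0.01, 10% to 16% at ICC 0.02, and 16% to 29% at ICC 0.05. The direction follows from any positive within-unit correlation. The size rests on the assumed ICC, equal unit sizes and the 5% level, and on a one-factor comparison rather than the full multiple regression. The finding does not extend to most person-level covariates, nor to overall seroprevalence within the four facilities.

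**What to change.** In section 3.1, state that the logistic models include a random intercept for working unit and a fixed effect for facility (four facilities are too few for a random effect). Alternatively, use unit-clustered standard errors with a small-sample correction. Cluster on working units and not on the 12 facility-by-area cells, which are too few for the usual robust standard error. Record each participant's working unit and report the estimated ICC. Reword the section 3 sentence so that *multi-level* refers to this model, and describe the handling of incomplete results separately. Cluster-adjusted intervals for overall seroprevalence are needed only if the result is generalised beyond the four facilities.

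The cost is a few sentences and one identifier that the recruitment rota already implies; Stata, the stated package, supports these methods. The statistical price is wider intervals for exposure-area effects: at ICC 0.02 with 20 to 50 staff per unit, √1.38 = 1.17 to √1.98 = 1.41, or about 17% to 41% wider. Settle this before analysis, so that the variance method is not chosen after the results are seen.

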### 2.5. Independent Variables

The selection of the parameters (included in the questionnaire) is based largely on the body of evidence from international literature on factors that influence or increase the risks of acquisition of SARS-CoV-2, severe COVID-19 disease, humoral immune response, and perception about vaccines [3,5,9,15,16,18]. Trained research nurses (without any affiliation to the study sites) will measure the height, weight, and mid-upper arm circumference according to standard protocols and the body mass index will be derived.

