### 2.9. Possible Outcomes

SARS-CoV-2 serology results will be matched with the baseline results of SARS-CoV-2 RT-PCR if previously done.

The following categories will emerge:Both SARS-CoV-2 RT-PCR and SARS-CoV-2 serology are positive: COVID-19 diagnosis confirmed, and humoral immune response is present.SARS-CoV-2 RT-PCR is positive but SARS-CoV-2 serology is negative: COVID -19 diagnosis confirmed but there is no persistent humoral immune response or too early for antibody detection.SARS-CoV-2 RT-PCR not done or negative but SARS-CoV-2 serology is positive: COVID-19 diagnosis was missed by PCR but there is a humoral immune response present.Both SARS-CoV-2 RT-PCR and SARS-CoV-2 serology are negative: no confirmed infection with SARS-CoV-2.

All participants will receive their results within a month of the study from designated persons (Occupational Health Champions) at each study site. Additional interventions (clinical consultations and/or psychologist’s or Employee Assistant Programme practitioner’s referral) will be available for HCWs with specific needs.

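### The infection risk-factor model classifies everyone without a positive PCR by a single IgG result, so factors that affect IgG persistence can appear as risk or protective factors for infection, and no planned analysis tells the two apart

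*Protocol article*

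**What the plan says.** Section 3.1 of the protocol article defines the modelled outcome: "The cumulative outcome (positive result obtained by either or both of SARS-CoV-2 RT-PCR and serology". Univariate models come first, followed by multivariable logistic models intended to "identify factors that are independently and significantly associated with the outcome measures". On covariates it states: "All variables will be included in the logistic regression model". The one sensitivity analysis described there uses complete data and addresses missing values.

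Section 2.9 shows how results are read. The category "SARS-CoV-2 RT-PCR not done or negative but SARS-CoV-2 serology is positive" is treated as an infection that PCR missed. A participant negative on both tests has no confirmed infection. For a positive PCR with negative IgG, the reading is that "there is no persistent humoral immune response or too early for antibody detection". The protocol thus accepts that IgG can be absent after a confirmed infection.

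Section 2.5 says questionnaire items were chosen from literature on "factors that influence or increase the risks of acquisition of SARS-CoV-2, severe COVID-19 disease, humoral immune response, and perception about vaccines". Section 2.12 lists factors for infection and factors for durable IgG as separate main outcomes. The Abstract says the logistic models will identify independent risk factors for infection.

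**The concern.** For a participant without a positive PCR, the outcome is in effect having been infected and still carrying detectable IgG on the day of the survey. The Introduction notes that PCR is often limited to people with symptoms, so mild and asymptomatic infections rest mainly on serology. If a covariate changes how long IgG stays above the assay cut-off, past infections are detected with different probability at different levels of that covariate. This is differential outcome misclassification. Adjusting for the covariate does not remove it, because the covariate itself drives detection.

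The covariate set covers acquisition and humoral response together, so the same variable can plausibly act on either. A factor that prolongs IgG would look like an infection risk and one that shortens it would look protective. A real risk that also shortens IgG could be hidden. The Abstract and Conclusions say that the findings will inform policy on protecting staff and may guide personnel allocation, so confusing more infection with longer antibody persistence would have practical consequences.

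**Working it through.** The article gives no numerical target for this model, so there is no stated figure to reproduce. The nested-cohort size of 201 plays no part here.

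**Inputs from the document**
- 2250 healthcare workers (Abstract, section 2.2). Two equal covariate groups would have 1125 each.
- 45% infected, the planning value in section 2.10.
- The 100% assay sensitivity in section 2.11 applies at 17 days after symptom onset and 13 days after PCR positivity, not months later.
- On durability, the Introduction cites one report with an IgG half-life of 36 days and another with IgG sustained to four months. Section 2.10 says most studies saw significant decline by three to four months.

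**Assumptions (not in the document)**
- 20% infected as a lower alternative.
- Share of infections known by PCR, d: 30%, with 60% as an alternative.
- Probability s of still being IgG positive among infected people without a positive PCR: 90% in one group against 85%, 75% or 60% in the other.
- True infection proportion p equal in both groups, so the true odds ratio is 1.00. False positives are ignored.

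**Formulas**
- Composite positivity: P = p × [1 − (1 − d)(1 − s)].
- Odds ratio: [P₁/(1 − P₁)] / [P₀/(1 − P₀)].
- Chance of p < 0.05: from the Wald z for log OR, with SE = √[1/(nP₁) + 1/(n(1 − P₁)) + 1/(nP₀) + 1/(n(1 − P₀))] and n = 1125.

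**Worked example** (p = 0.45, d = 0.30, s = 0.90 against 0.60)
- P₁ = 0.45 × (1 − 0.70 × 0.10) = 0.4185.
- P₀ = 0.45 × (1 − 0.70 × 0.40) = 0.3240.
- OR = (0.4185/0.5815)/(0.3240/0.6760) = 1.50.
- SE = 0.0878 and z = 0.4065/0.0878 = 4.63, so the result is significant in over 99% of studies.

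| Infected | Known by PCR | IgG retained | Composite positive | Spurious OR | Chance of p < 0.05 |
|---|---|---|---|---|---|
| 45% | 30% | 90% v 85% | 41.9% v 40.3% | 1.07 | 12% |
| 45% | 30% | 90% v 75% | 41.9% v 37.1% | 1.22 | 63% |
| 45% | 30% | 90% v 60% | 41.9% v 32.4% | 1.50 | over 99% |
| 20% | 30% | 90% v 85% | 18.6% v 17.9% | 1.05 | 7% |
| 20% | 30% | 90% v 75% | 18.6% v 16.5% | 1.16 | 26% |
| 20% | 30% | 90% v 60% | 18.6% v 14.4% | 1.36 | 76% |
| 45% | 60% | 90% v 75% | 43.2% v 40.5% | 1.12 | 25% |
| 20% | 60% | 90% v 75% | 19.2% v 18.0% | 1.08 | 11% |

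The nominal rate is 5%. With groups of 450 and 1800 instead of 1125 each, the 63% falls to about 45%. Swapping the groups inverts the odds ratio: 1.50 becomes 1/1.50 = 0.67, an apparent protective factor.

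A second calculation added the 99.9% specificity from section 2.11 and used a wider grid: 10% to 45% infected, 20% to 60% known by PCR, and retention gaps of 5 to 40 points. The odds ratio was above 1 in every scenario, from 1.02 to 1.91.

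**The case against.** The strongest reply is that the documents give no difference in IgG retention between covariate groups, so every odds ratio above rests on an assumption. With a 5-point gap the artefact is barely visible. If IgG is sustained to four months, as the larger report in the Introduction found, it could be negligible. This stands, and it limits the claim to a possibility of unknown size.

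A reader might infer that any factor altering IgG persistence will be reported as a risk factor for infection. The documents do not support that. Whether such a factor reaches significance depends on the retention gap, PCR coverage, prevalence and group sizes, and a factor that shortens IgG would look protective. A reader might also infer that the protocol itself expects serology to miss infections unequally across covariates. It only makes durability factors a question to be studied and calls durability unclear.

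Two further replies have some force. Section 3.1 itself speaks of association with an openly defined outcome; the infection-risk reading comes from the Abstract and section 2.12, so part of the defect is labelling. The composite also keeps PCR-positive, IgG-negative staff as cases, and sections 2.8 and 3 provide for searching laboratory and occupational health records. That reduces the bias, but only for people who were tested.

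It can also be said that a correction model belongs in a fuller plan. However, section 3.1 already fixes the outcome, the model, the covariate rule and a sensitivity analysis, and that analysis addresses a different problem.

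**Conclusion.** The concern holds as a limit on interpretation. Under the outcome in section 3.1, an association can reflect more infection, longer antibody persistence, or both, and nothing described separates them. The direction of the bias follows from the outcome definition once some infected people without a positive PCR have lost IgG and the covariate affects that loss.

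The size cannot be fixed from the documents. With 30% of infections known by PCR and equal groups, the spurious odds ratio runs from about 1.05 to 1.50 over the assumed retention gaps and the two infection levels. With 60% known by PCR, the 90% against 75% case falls to 1.12 or 1.08. The article itself calls durability unclear, which is a reason to build in the check and not to assume the effect is absent.

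**What to change.** In section 3.1:

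1. Name the outcome as evidence of past infection (PCR or IgG positive), and use that name in the Abstract and section 2.12 when describing the model.
2. For the main covariates, add a misclassification sensitivity analysis. Among people without a positive PCR, vary the sensitivity of serology by covariate level over a stated range, and report the odds ratio across that range. Anchor the range on the share of PCR-confirmed participants with IgG present at each covariate level. Section 3.2 already plans to evaluate IgG in this group, so only the split by covariate is new.
3. Do not assign a time since PCR to people without a positive PCR, because they have no such date. Fine cells would also be too small. At 20% infected and 30% known by PCR there are 2250 × 0.20 × 0.30 = 135 PCR-confirmed staff. A binary covariate by three time bands leaves about 22 per cell, and a sensitivity of 75% is then known only to about ±1.96 × √(0.75 × 0.25/22.5) = ±18 points.
4. Describe a factor as an infection risk factor only with this analysis reported beside it. Where the association does not hold across the plausible range, report it as associated with PCR or IgG positivity, and state that differential antibody persistence cannot be excluded.

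The cost is one added analysis on data already planned. The conclusions will be wider or less definite. Sensitivity learned in PCR-confirmed, mostly symptomatic staff may also be optimistic for asymptomatic infections. The range should therefore extend below the observed values, and the limitation should be stated.
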